### *Comparison of ICECAP-A, EQ-5D-5L and SF-36 outcomes*

As described above, ANCOVA models will be fitted to determine whether patients significantly improved (a p-value below 0.05) in terms of ICECAP-A, EQ-5D-5L and SF-36 scores. Multiple contingency tables will be created to compare the number of patients that

are responder or non-responder based on the ICECAP-A, EQ-5D-5L and SF-36 ANCOVA models. These comparisons will be performed both for the non-weighted scores and the preference-weighted scores. An analysis solely based on the preference-weighted scores may conclude that the measure is not responsive, when in fact, it could be that the descriptive system of the measure is responsive but the change is not valued.

To calculate the EQ-5D-5L preference-weighted scores the Dutch reference values will be used (Versteegh et al., 2016).

ICECAP-A preference-weighted scores will be calculated using the algorithm from Flynn et al. (Flynn et al., 2015).

Based on a selection of SF-36 items, the SF-6D can be derived. The SF-6D is composed of six multi-level dimensions, and any patient who completes the SF-36 can be uniquely classified according to the SF-6D. The SF-6D provides a means for using the SF-36 in health economic evaluation by estimating a preference-based index value based on preference weights obtained from a sample of the general population. Because no Dutch reference values are available, the preference weights derived from the UK population will be used (Gerhards et al., 2011).

In addition, an anchor-based analysis will be performed to explore whether ICECAP-A scores change in the expected direction as indicated by changes in the EQ-5D-5L and SF-36 scores. Both the EQ-5D-5L and SF-36 scores will be used to divide the patients into groups: (1) patients that worsened; (2) patients that showed no significant change; (3) patients that improved; and within these groups the mean ICECAP-A changes will be used to see whether they show the same direction of change (Keeley et al., 2015).

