### Secondary Objectives:

- To develop rehabilitation care for patients with NMD that is based on the capability approach.
- To assess treatment fidelity in designing capability care, training of the health care professionals in providing capability care, delivery of capability care, and receipt and enactment of capability care by the patients with NMD.
- To determine how capability care, in comparison to usual care, facilitates changes in resources and conversion factors, enlarging functionings and capabilities.
- To compare the capabilities outcome of patients with NMD receiving capability care versus usual care, using the ICECAP-A that covers five attributes (e.g. attachment, stability, achievement, enjoyment, autonomy) of wellbeing.
- To compare the participation outcome (USER-P) of patients with NMD receiving capability care versus usual care.
- To compare the work capabilities outcome (CSWQ) of patients with NMD receiving capability care versus usual care.
- To determine whether the use of a broader measure of quality of life (ICECAP-A), compared to a health-related quality of life measure (EQ-5D-5L, SF-36), leads to other outcomes in terms of assessing the benefits of care.

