| To determine whether the use of a broader measure of quality of life (ICECAP-A), compared to a health-related quality of life measure (EQ-5D-5L, SF-36), leads to other outcomes in terms of assessing the benefits of care | ICECAP-A usual care
ICECAP-A capability care

EQ-5D-5L usual care
EQ-5D-5L capability care

SF-36 usual care
SF-36 capability care | Multiple comparisons between usual care group and capability care group on difference T1-T0.                                                                       | ANCOVA, contingency table         |

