### *Statistical analysis*

Data will be visualised using scatter-plots, box plots and histograms. Descriptive statistics will include mean and standard deviation. To answer the primary research question, whether there is a difference in improvement at T1 between the capability care and usual care group, an ANCOVA model will be fitted. Covariates will be the T0 scores of both groups, age, gender and diagnosis. With the model it is tested whether an intervention-effect is present. For an intervention-effect to be present, the scores on both the COPM-P and COPM-S will need to show a significant change. A p-value below 0.05 will be considered significant.

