## 8.2 Secondary study parameters

For the following secondary study parameters, similar analyses as described above (ANCOVA model) will be performed:

- ICECAP-A preference-weighted index score
- ICECAP-A non-weighted sum score
- USER-P
- CSWQ total score
- EQ-5D-5L preference-weighted index score
- EQ-5D-5L non-weighted sum score
- SF-36 preference-weighted index score
- SF-36 non-weighted sum score

The CSWQ overall question will be analysed using a Mann-Whitney U test. Median and range will be described. The Mann Whitney U test will be performed on the difference score between T1 and T0, to determine whether there is a difference between the usual care and capability care group. A p-value below 0.05 will be considered significant.

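### Section 8.2 takes each patient's responder status from between-group ANCOVA models that give no patient a status, so the responder contingency tables are undefined as written

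*Protocol*

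**What the plan says.** One secondary objective in Protocol section 2 begins "To determine whether the use of a broader measure of quality of life (ICECAP-A), compared to a health-related quality of life measure (EQ-5D-5L, SF-36", and asks whether the choice of measure changes the conclusion about benefit.

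Section 8.1 defines the model. "Covariates will be the T0 scores of both groups, age, gender and diagnosis", and its purpose is stated plainly: "With the model it is tested whether an intervention-effect is present". Section 8.2 lists the ICECAP-A, EQ-5D-5L and SF-36 scores, preference-weighted and non-weighted, among those for which "similar analyses as described above (ANCOVA model) will be performed".

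The later part of section 8.2, on comparing the three instruments, has three strands:

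- Models: "ANCOVA models will be fitted to determine whether patients significantly improved (a p-value below 0.05".
- Contingency tables of patients who "are responder or non-responder based on the ICECAP-A, EQ-5D-5L and SF-36 ANCOVA models", for both kinds of score.
- An anchor-based analysis that sorts patients by their change on EQ-5D-5L and SF-36 and examines mean ICECAP-A change in each group. The middle group is "2) patients that showed no significant change".

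The last row of Table 5 gives the analysis for this objective as "Multiple comparisons between usual care group and capability care group on difference T1-T0" and names ANCOVA and a contingency table as the test.

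**The concern.** Section 8.2 gives the ANCOVA two tasks that section 8.1 does not equip it for. The first is to show improvement in patients. A between-group p-value is silent on that: both groups may have declined, one less than the other, which is a real possibility in conditions the protocol itself calls progressive. The second is to supply a label for each patient. The model as specified has no such output, so the tables have no defined input.

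This is more than a detail that a statistical analysis plan would fill in. The protocol is not silent on where responder status comes from. It names the source, and an analysis plan that followed it would inherit a rule that does not work. If the analyst improvises instead, the responder cut-off may be chosen after the data are seen. If the tables are dropped, it becomes tempting to judge the instruments by which of them reaches p < 0.05, which is not a test of whether they differ.

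**Working it through.** **The plan's own figures.** None is given for the responder analysis. The only related calculation is the COPM sample size in section 4.4, and it reproduces. The residual SD is 1.9 × √(1 − 0.5²) = 1.645. With a two-sided 0.05 level and noncentral-t power, COPM-P alone has power 0.806 at 23 per group. The product of the COPM-P and COPM-S powers is 0.781 at 23 and 0.802 at 24. The stated 23 and 24 stand and have no bearing on this point.

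**What the model returns.** For patient i, section 8.1 amounts to

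T1ᵢ = β₀ + β₁·groupᵢ + β₂·T0ᵢ + (age, gender, diagnosis terms) + eᵢ.

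The test is of β₁: one estimate and one p-value per score, with no status attached to any patient.

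**Why the p-value cannot carry improvement or response.** Add a constant k to every T1 score. Only β₀ changes, to β₀ + k. The estimate of β₁, its standard error and its p-value are identical. Yet every patient's T1 − T0 has moved by k. With k low enough, both groups have worsened on average while the group effect is just as significant as before.

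**Illustration.** The protocol gives no SD, effect or cut-off for ICECAP-A, EQ-5D-5L or SF-36, so these inputs are assumptions: SD 1, T0-T1 correlation 0.5, 30 per group, and a true effect of 0.74 SD, which is the COPM-P design value 1.4/1.9 from section 4.4. The model has group and T0 only. In one simulated data set p = 0.029. Responders (T1 − T0 at or above the cut-off) were:

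| Shift added to all T1 | Cut-off (SD) | p | Usual care (of 30) | Capability care (of 30) |
|---|---|---|---|---|
| 0 | 0 | 0.029 | 13 | 21 |
| 0 | 0.2 | 0.029 | 10 | 19 |
| 0 | 0.5 | 0.029 | 9 | 15 |
| 0 | 0.8 | 0.029 | 7 | 11 |
| 0 | 1.0 | 0.029 | 4 | 7 |
| −0.5 SD | 0.5 | 0.029 | 4 | 7 |
| +0.5 SD | 0.5 | 0.029 | 13 | 21 |

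The p-value is the same in every row and the counts are not.

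**Expected shares.** Under the same assumptions the change has SD √(1 + 1 − 2 × 0.5) = 1. With no average change in usual care and an effect d in capability care, the responder share at cut-off c is 1 − Φ(c) in usual care and 1 − Φ(c − d) in capability care. For c = 0, 0.5 and 1, usual care gives 50%, 31% and 16%. Capability care with d = 0.74 gives 77%, 59% and 40%. The cut-off, which the protocol does not state for these measures, drives the result. The only patient-level cut-offs in the document are for the COPM (1.35 and 1.90, section 6.1.1).

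**The anchor groups.** These are formed from score changes, not from the ANCOVA, so they do not inherit the wrong source. What they lack is a stated boundary for the middle group.

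**Table 5, last row.** A between-group comparison of T1 − T0 is legitimate. With T0 as covariate, it gives the same group effect as ANCOVA on T1. The row needs changing only because it repeats the contingency table without a patient-level rule.

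**The case against.** The strongest reply is that the objective does not rest on these tables. The per-instrument ANCOVAs can be run as specified and yield adjusted effects for each measure, and the anchor-based analysis is a separate route. That stands. A reader might infer that the whole objective cannot be answered as written, or that the responder tables are its only analysis; section 8.2 contradicts both.

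Second, a fitted regression can support individual classification, for instance through residuals or prediction limits with a threshold, and an individual's change can be judged against measurement error. That also stands, so the accurate word is undefined, not impossible. But the protocol specifies none of these.

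Third, a cut-off may sit in an analysis plan that is not shown. For the anchor groups this is fair, and the missing number alone is no finding. It does not rescue the responder sentence, which states a source that does not work.

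Fourth, a reader might infer that the instruments will falsely appear to disagree about half the time. That rests on a decision rule (do the instruments differ in reaching significance) which the protocol never states, and on assumed power and correlation. For three tests with equal true effects, disagreement is 1 − 2 × 0.5³ = 75% at 50% power if the tests are independent. If the statistics correlate 0.6, it is 44% at 50% power, 30% at 20% or 80% power, 18% at 10% or 90%, and 10% at 5%. At correlation 0.8 it never exceeds 31%. The protocol gives neither power nor correlation for these measures, and 50% power is the worst case. These figures warn against reading p-values that way; they do not measure a defect in this plan.

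**Conclusion.** The responder contingency tables cannot be built from the rule stated in section 8.2, and that section misdescribes a between-group test as a test of improvement. This follows from the protocol's own definition of the ANCOVA and needs no numerical assumption; the simulated counts only illustrate it.

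The reach is limited to the patient-level responder comparison within one secondary objective. The group-level ANCOVAs for the three instruments remain valid as between-group comparisons, and the anchor-based analysis remains usable once its cut-off is fixed. The primary COPM analysis, its success criterion and its sample size are unaffected. It should be corrected before outcomes are analysed, but it does not threaten the main result.

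**What to change.** In section 8.2 and the last row of Table 5:

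1. State that each ANCOVA tests the between-group difference at T1 adjusted for T0 and the other covariates, and does not test whether patients improved.
2. Replace the ANCOVA as the source of responder status with a prespecified patient-level rule on T1 − T0. Use one type of rule for all instruments (for example a fixed fraction of the pooled T0 SD), for both non-weighted and preference-weighted scores. Use the same rule to form the worsened, unchanged and improved anchor groups.
3. Cross-tabulate ICECAP-A against EQ-5D-5L, and ICECAP-A against SF-36/SF-6D, within the same patients, and analyse the tables as paired data. State that a difference between instruments will not be inferred from which p-value falls below 0.05.

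Any such threshold is partly conventional, so results at one alternative threshold should be shown. The particular fraction and agreement statistic are the sponsor's choice, provided they are fixed before the data are examined. The cost is rewording one section and one table row; no new data are needed.

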### **8.3 Other study parameters**

The other study data collected will be used for the development of capability care and for the process evaluation. Figure 4 (see chapter 6) gives an overview of the process evaluation. In this chapter the analyses that will be performed are described.

#### **8.3.1 Developing capability care**

For the development of capability care (as described in chapter 5.1.2), a qualitative analysis will be performed on data collected in the usual care group. The data that will be used are the consultations with the health care professionals (audio recorded), the multidisciplinary team meetings (audio recorded), the medical reports (from the patient files) and the interview with patients (and partners) at 6 months follow up.

The consultations with health care professionals and the multidisciplinary team meetings will be audio recorded. A random selection of these recordings will be transcribed; relevant fragments will be selected by two researchers independently and discussed until agreement has been reached. If the researchers find a large variation between the selected records, a new random selection will be added for analysis to determine whether this is a true variation or a variation because of the selection process. The medical reports are written; they will be obtained from the electronic patient record system (EPIC) that is used at Radboudumc. Relevant information from the medical reports will be selected by two researchers independently and discussed until agreement has been reached.

The qualitative analysis of the selected fragments and medical reports consists of the following steps:

- 1) Codes will be allocated to meaningful text parts answering the research questions by two independent researchers. This coding will be done using the program Atlas-Ti.
- 2) The researchers will discuss codes and categories.
- 3) The codes and categories are discussed with the whole research group and overarching themes may be discussed.
- 4) Themes and subthemes are formulated and illustrated with original quotes.

For the interviews with patients and, if possible, their partners, a constant comparative method (Evers, 2016) will be applied using the following alternating steps:

- 1) 3 to 5 interviews will take place with patients and partners and will be audio-recorded
- 2) The interviews will be transcribed ad verbatim and field notes of the relevant observations from the audio recordings will be made. After reading the interviews, codes will be allocated to meaningful text parts answering the research questions. This coding will be done using the program Atlas-Ti.
- 3) The researchers will discuss codes and insights and discuss whether new insights are topics to be addressed in the next interviews.
- 4) Another 3-5 interviews are being held and transcribed, coded and discussed and some initial categories are being discussed.
- 5) The final 5-10 interviews are being held, transcribed and coded and evaluated whether these confirm the preliminary categories or whether new categories arise. New patients and partners are interviewed and coded and categorized until no new categories arise.
- 6) The codes and categories are discussed with the whole research group and overarching themes may be discussed.
- 7) Final themes and subthemes are formulated and illustrated with original quotes.

The information obtained through qualitative analysis will be used for discussions within the project team, with health care providers and with experts from the capability approach field to develop capability care (as described in chapter 5.1.2).

### **8.3.2 Assessment of treatment fidelity**

An intervention may have limited effects or positive outcomes because of weaknesses in its design or because it is not properly implemented. Therefore, a process evaluation should capture fidelity: was the intervention delivered as intended?

To assess treatment fidelity (delivery of capability care and receipt and enactment of capability care), both a qualitative and quantitative analysis will be performed. Information on delivery of capability care will be derived from the audio recordings of consultations and team meetings, medical reports, and focus groups with healthcare professionals. Information on receipt and enactment of capability care will be derived from the interview with patients and, if possible, partners.

The method for the qualitative part of the analysis to assess treatment fidelity has been described above (chapter 8.3.1.); however, when using this information for assessment of treatment fidelity, we will use data from both the usual care and capability care group to conduct the analysis as described above. The information obtained through this analysis will

provide the information needed to assess treatment fidelity qualitatively because it retrieves and analyses information on the delivery, receipt and enactment of care.

#### *Capability scoring form*

The quantitative part of the analysis to assess treatment fidelity (delivery of capability care) will be performed as described below.

When developing capability care, a scoring form for delivery of capability care will be developed. This 'capability scoring form' will include treatment elements based on the capability approach (e.g. resources, conversion factors, functionings) and the seven capability dimensions used by Alkire (2002). These dimensions are: (1) life, health; (2) knowledge; (3) aesthetic experience; (4) play; (5) sociability (friendship); (6) practical reasonableness; (7) religion or transcendence.

The elements in this form will be classified into (1) essential and unique; (2) essential but not unique; (3) compatible but not essential and not unique; (4) prohibited; and (5) unique but not essential (Leeuw, Goossens, de Vet, & Vlaeyen, 2009). A scoring form can be constructed by scoring the treatment elements on whether or not they did occur, or on how often they did occur (e.g. on a likert scale or counting of elements). Depending on the development of capability care, it will be determined which treatment elements will be included and what scoring system is most suitable for these elements.

Two blinded research assistants will independently score a random selection (from usual care and capability care) of the consultations with the health care professionals, multidisciplinary team meetings and medical reports using the 'capability scoring form'. Interrater reliability, protocol adherence, treatment contamination and treatment differentiation (Leeuw et al., 2009) will be calculated. The exact calculation method needs to be determined based on the scoring system used (e.g. dichotomous scoring, likert scale, counting of elements). Besides assessing treatment fidelity, the obtained scores will also be used to determine the extent to which usual care and capability care differ.

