#### 5.1.2 Capability care

##### *Development of capability care*

As recommended by the Medical Research Council (Moore et al., 2014, 2015), there needs to be a clear description of the intervention and its causal assumptions before implementing the intervention. To develop the capability application in healthcare ('capability care') for patients with neuromuscular diseases, we will use a combination of theoretical exploration,

discussions within the project group and with other experts from the capability approach domain and the rehabilitation field, and using insight obtained by analysing the data collected from the usual care group.

After 6 months, the usual care group will be followed up, where one of the measures is a retrospective interview. This interview focuses on how the patients have experienced the healthcare and how this has changed several aspects in their lives, and on the limitations and barriers that prevent making these changes (see interview guide in appendix F; outcome measures). These interviews will be qualitatively analysed in terms of the capability approach. Additionally, the consultations with the health care professionals (audio-recorded), the multidisciplinary team meetings (audio-recorded) and the medical reports from the patient files will be analysed qualitatively in terms of the capability approach. This step is needed to determine in what respect usual care can be improved when looking through the capability lens. The results of this qualitative analysis will be discussed within the project team, with the health care providers and with experts from the capability approach field, to determine the changes that need to be made to provide capability care (development of the capability care intervention) and provide a clear description of the intervention and its causal assumptions.

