#### Medical reports

All medical reports (including reports from e.g. allied health professionals and nurses) from the departments of neurology and rehabilitation during the inclusion period of the patient will be analysed, to determine the delivery of capability care (an aspect of treatment fidelity) and in what respect capability care differs from usual care. The medical reports will be obtained from the electronic patient file (EPIC) and will be analysed in terms of the capability approach and based on the seven capability dimensions used by Alkire (2002). These dimensions are: (1) Life, health; (2) Knowledge; (3) Aesthetic experience; (4) Play; (5) Sociability (friendship); (6) Practical reasonableness; (7) Religion or transcendence. The analysis is described in more detail in paragraph 8.3.

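### Usual-care records that help shape the capability scoring form are not kept out of the sample scored with it, so the difference between the two kinds of care may be overstated

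*Protocol*

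**What the plan says.** Section 5.1.2 builds capability care from theory, discussion with experts and "using insight obtained by analysing the data collected from the usual care group". It gives the purpose of studying the usual-care consultations, team meetings and medical reports: "This step is needed to determine in what respect usual care can be improved when looking through the capability lens". Section 8.3.1 repeats that "a qualitative analysis will be performed on data collected in the usual care group". For recordings it takes a random selection of unstated size, to be enlarged if the selected records vary widely. For medical reports it names no subset.

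Section 8.3.2 says of the form: "When developing capability care, a scoring form for delivery of capability care will be developed". The form "will include treatment elements based on the capability approach (e.g. resources, conversion factors, functionings) and the seven capability dimensions", but its content stays open: "Depending on the development of capability care, it will be determined which treatment elements will be included and what scoring system is most suitable". Elements are sorted into five classes, among them essential and unique, essential but not unique, and prohibited. Two blinded research assistants then score a random selection of consultations, team meetings and medical reports from both groups. Inter-rater reliability, adherence, contamination and differentiation are calculated, and the section adds: "Besides assessing treatment fidelity, the obtained scores will also be used to determine the extent to which usual care and capability care differ".

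**The concern.** The usual-care records have two roles. They are searched for what usual care lacks, which helps decide what the form contains, and they are then eligible to be scored with that form. An element may be included, or classed as unique to capability care, partly because it was seldom seen in the records studied. It will then tend to score lower in those records than in usual care generally. This is ordinary selection optimism, and it acts in one direction: usual care looks less like capability care than it is.

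Treatment fidelity is a stated secondary objective (section 2), and section 6.1 relies on the process evaluation to explain the outcome results. The groups are sequential and not randomised, so this contrast is the planned quantitative evidence of how far the care changed. If it is overstated, the two kinds of care appear more distinct than they were.

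**Working it through.** The protocol gives no figure for this comparison: no number of elements, no number of records and no expected score. There is nothing to reproduce. The check has two parts.

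**1. Tracing the text**
- The usual-care records are studied for possible improvements (sections 5.1.2 and 8.3.1).
- The choice of elements and of the scoring system waits on that development (section 8.3.2).
- The scored usual-care records are a random selection from the same group (section 8.3.2).
- No section excludes the development records from that selection.

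If the development and scoring selections are drawn independently, the expected share of scored usual-care records already used in development equals the share of the pool used in development. Some overlap is therefore the expected result, but its extent is not fixed.

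**2. Illustrating the size**

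Let *b* be the average shortfall of the chosen elements when the development records themselves are scored, and *s* the share of scored usual-care records that come from development. The expected spurious difference is *s* × *b*. It is zero if *s* = 0 (no overlap) or *b* = 0 (elements not chosen from the data).

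To put numbers on *b*, 1,500 runs per setting were simulated with no true difference between the two kinds of care. All inputs are assumptions:
- 20 candidate elements with mean frequency 0.3, either all equal or varying as Beta(3, 7) or Beta(1.5, 3.5).
- 10, 20 or 30 development records.
- The 10 or 15 elements seen least often in those records are kept.
- For comparison, a theory-fixed list in which all 10 of 10 elements are kept.
- 10 usual-care records are scored when there are 10 development records, and 20 otherwise.

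Selected results, as capability-care minus usual-care element frequency (0 to 1 scale):

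| Elements kept | Frequencies | Development records | No overlap | Half overlap | Full overlap |
|---|---|---|---|---|---|
| 10 of 20 | equal | 10 | 0.001 | 0.056 | 0.109 |
| 10 of 20 | equal | 30 | 0.001 | 0.031 | 0.066 |
| 10 of 20 | Beta(3, 7) | 20 | 0.001 | 0.022 | 0.043 |
| 15 of 20 | Beta(1.5, 3.5) | 30 | 0.000 | 0.007 | 0.012 |
| 10 of 10 (fixed list) | equal | 10 | -0.002 | 0.002 | -0.001 |

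The first row agrees with the formula: 0.5 × 0.109 = 0.055, against 0.056 simulated. Over all settings with data-driven choice, full overlap gives 0.012 to 0.109 and half overlap 0.007 to 0.056. With no overlap, or with a fixed list, every result lies within 0.002 of zero.

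**The case against.** A reader might infer that the form is derived from the usual-care records and that the difference is therefore inflated by construction. The protocol does not support that. The stated source of the elements is the capability approach and seven published dimensions; usual-care data enter indirectly, as one of several inputs to capability care. No rule labels an element unique because it was rare, and the coding in section 8.3.1 yields themes, not counts. The simulation's selection rule is thus a stand-in for a looser judgement. Inflation needs both data-driven choice and overlapping records, and neither is certain. A form with elements unique to capability care is also meant to separate the two kinds of care, so a large difference is not in itself a bias.

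A reader might also infer from section 6.1.3, which has "All medical reports (including reports from e.g. allied health professionals and nurses) from the departments of neurology and rehabilitation" analysed, that no untouched usual-care report remains. That sentence describes the analysis of delivery and of differences between the two kinds of care, not the building of the form.

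Nor does it follow that undelivered capability care would pass as delivered. Capability-care records do not exist when the form is made, so adherence scored on them is not biased by this route. Delivery is also judged from qualitative analysis of both groups and from focus groups.

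These points limit the concern but do not remove it. Blinded raters protect the scoring; they cannot undo an earlier choice of elements. Separation is a fair finding only on records that did not help choose the elements. Nor can this wait for a later analysis plan: the protocol already states what is sampled for scoring, and once development has used the records, untouched ones cannot be restored.

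**Conclusion.** The concern holds in limited form. Usual-care scores can be too low and treatment differentiation too high, because form content stays open while usual-care records are studied and the same group is then scored without excluding those records. The direction is known and the size is not. With no true difference, the illustration gives about 0 if either condition is absent, about 0.01 to 0.06 at half overlap and about 0.01 to 0.11 at full overlap. These figures rest on assumed numbers of elements and records, an assumed mean frequency of 0.3, and selection by observed rarity. The point concerns a secondary process measure. Adherence scored in capability care does not change, and the COPM ANCOVA in section 8.1 does not use the form.

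**What to change.** - **Section 8.3.1:** before development starts, draw at random a subset of usual-care patients whose recordings, team meetings and medical reports will not be used to develop capability care or the form. If a further selection is needed because records vary, take it from the other patients.
- **Split by patient, at random, and not by interview status.** Interviews run until saturation, so the interviewed patients cannot be listed in advance, and non-interviewed patients may differ from the rest. Interviews are not scored with the form, so their sampling can stay as planned.
- **Section 8.3.2:** fix the elements, their classes and the scoring rules before any set-aside record is opened. Draw the usual-care records for scoring from that subset, and compare them with a random selection of the same record types from capability care.
- **Fallback:** if no subset can be set aside, report development and non-development usual-care records separately.

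The cost is a few sentences and one patient list. Somewhat fewer usual-care records are available for development, which for recordings already uses only a random selection, and fewer are available for scoring. The set-aside reports can still enter the analysis in section 6.1.3 once the form is fixed.
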